##### Qualitative Data Collection

To understand patient experience with CaVS recovery and involvement with the SMArTVIEW intervention, we will conduct telephone interviews with 60 patients and 60 primary support persons in the intervention and control groups and with all SVNs (n=20) using a semistructured interview guide. The interviews will focus on perceptions of usability and ethical, social, and legal issues. Our sample size should ensure data saturation [125].

##### Sample Size

Assuming a two-sided type I error (alpha) of .05 and a standard deviation of 20 points in BPI-SF numeric rating scale scores (range 0-100), a total of 128 participants (ie, 64 individuals in each group) are required to provide 80% power to detect a minimally important difference of 10 points. This difference represents a moderate effect size (Cohen’s d=0.50) [126]. Assuming a 10% loss to follow-up, 144 total patients (or 72 per group) is required. We will use this sample size for each site, to allow for site-specific analyses with equal and sufficient power. If there is sufficient homogeneity between the Canadian and UK samples, the combined sample (eg, 256 patients with complete data) would provide 80% power to detect a difference in pain intensity scores of 8.6 points (Cohen’s d=0.43), assuming a generous design effect [127] of 1.5 due to the clustering of participants within the site.

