**Methods:**

CaVS patients and clinicians will engage in two cycles of focus groups and usability testing at each site; feedback will be elicited about expectations and experience of SMArTVIEW, in context. The data will be used to refine the SMArTVIEW eHealth delivery program. Upon transfer to the surgical ward (ie, post-intensive care unit [ICU]), 256 CaVS patients will be reassessed postoperatively and randomly allocated via an interactive Web randomization system to the intervention group or usual care. The SMArTVIEW intervention will run from surgical ward day 2 until 8 weeks following surgery. Outcome assessments will occur on postoperative day 30; at week 8; and at 3, 6, 9, and 12 months. The primary outcome is worst postop pain intensity upon movement in the previous 24 hours (Brief Pain Inventory-Short Form), averaged across the previous 14 days. Secondary outcomes include a composite of postoperative complications related to hemodynamic compromise—death, myocardial infarction, and nonfatal stroke— all-cause mortality and surgical site infections, functional status (Medical Outcomes Study Short Form-12), depressive symptoms (Geriatric Depression Scale), health service utilization-related costs (health service utilization data from the Institute for Clinical Evaluative Sciences data repository), and patient-level cost of recovery (Ambulatory Home Care Record). A linear mixed model will be used to assess the effects of the intervention on the primary outcome, with an a priori contrast of weekly average worst pain intensity upon movement to evaluate the primary endpoint of pain at 8 weeks postoperation. We will also examine the incremental cost of the intervention compared to usual care using a regression model to estimate the difference in expected health care costs between groups.

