#### Feasibility

Our technology partners have contributed equipment and personnel time, in-kind, such that we are able to intervene and follow up on 15 patients at one time per site throughout the study until 30 days follow-up, at which time equipment will be returned to each hospital site for cleaning and reset. Therefore, the RCT (Phase 2) will be executed in five serial, parallel waves of approximately 30 patients per site. In 2014, there were 2311 and 1974 CaVS performed at Hamilton Health Sciences, Canada, and the Liverpool Heart and Chest Hospital, the United Kingdom, respectively. Planned recruitment will occur at a rate feasible for SVN time and access to the surgical populations at both sites. Patients will be enrolled during a 3-week period, with the last week of each recruitment month available for additional patient registrations as needed to accommodate those not meeting postop eligibility. Each site will target recruitment of 14 cardiac and 16 vascular patients during 3 weeks of recruitment—10 patients per week, per site. Allowing for a 25% refusal rate, lost opportunities, and competing studies, this still provides access to 20 patients at Hamilton Health Sciences and 17 patients at the Liverpool Heart and Chest Hospital. Since participant recruitment is only limited by prototype availability, our proposed recruitment target and timeline is feasible and recruitment of 300 participants will be completed in 10 months’ time.

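### The Abstract gives the completer count (256) as the number randomized where the Sample Size section implies 288, and the pooled 8.6-point detectable difference rests on a site design effect that does not fit individual randomization

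*Protocol article*

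**What the plan says.** The Sample Size section starts from "Assuming a two-sided type I error (alpha) of .05 and a standard deviation of 20 points" and finds that 128 patients, 64 per arm, "are required to provide 80% power to detect a minimally important difference of 10 points". It then allows for attrition: "Assuming a 10% loss to follow-up, 144 total patients (or 72 per group) is required. We will use this sample size for each site". The Settings section names two sites. The Sample Size section goes on to describe the combined sample, if the sites are homogeneous enough to pool. It gives 256 as the number with complete data and a detectable difference of 8.6 points (d = 0.43) at 80% power, "assuming a generous design effect [127] of 1.5 due to the clustering of participants within the site".

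The Methods part of the Abstract says instead that "256 CaVS patients will be reassessed postoperatively and randomly allocated". The Feasibility section plans five waves of about 30 patients per site and says that "recruitment of 300 participants will be completed in 10 months".

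The Trial Design section describes a two-group parallel trial. Under Randomization and Allocation, each consented patient who passes the ward screen is allocated individually, in blocks, through the web system.

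**The concern.** Two separate matters arise.

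First, 256 is the number randomized in the Abstract and the number completing in the Sample Size section. Both cannot hold when 10% loss is expected. The Abstract's version drops the attrition allowance, and the Sample Size section promises adequate power within each site, so following the Abstract would cost some of that power.

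Second, the pooled detectable difference divides the sample by 1.5 for clustering within site. That kind of inflation belongs to designs in which whole clusters are allocated to one arm. Here each site contributes patients to both arms. If the reason given does not apply, the only precision figure for the combined trial is wrong, and readers are told that the pooled comparison is less sensitive than it is.

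**Working it through.** **Inputs, all from the Sample Size section unless noted.** Two-sided alpha 0.05; power 80%; SD 20 on a 0-100 scale; difference 10 points; 1:1 allocation; loss 10%; two sites (Settings); 256 completers pooled; design effect 1.5.

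**Step 1: the per-site size reproduces.** With z-values 1.960 + 0.842 = 2.802, n per arm = 2 × 2.802² × (20/10)² = 62.8, so 63. The noncentral t gives 63.8, so 64 per arm and 128 per site, as stated. Attrition: 64/0.9 = 71.1, so 72 per arm and 144 per site, as stated. No design effect enters here.

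**Step 2: totals implied by the text.**

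| Quantity | Arithmetic | Total |
|---|---|---|
| Completers needed | 2 × 128 | 256 |
| Randomized (implied, not printed) | 2 × 144 | 288 |
| Completers from 288 | 288 × 0.9 | 259 |
| Recruited (Feasibility) | 5 × 30 × 2 | 300 |
| Randomized (Abstract) | as stated | 256 |

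**Step 3: consequence if the Abstract were followed.** 256 × 0.9 = 230.4 completers; 230.4/4 = 57.6 per arm per site. Power for 10 points (d = 0.50) by the noncentral t is 75.8%, against 80.1% with 64 per arm. The pooled detectable difference at 80% power would be 7.4 points without the design effect and 9.1 points with it.

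**Step 4: the pooled figure reproduces only with the 1.5.** Effective n per arm = 256/(2 × 1.5) = 85.3. Detectable d = 2.802 × √(2/85.3) = 0.429, and 0.429 × 20 = 8.58 points. The noncentral t gives d = 0.431 and 8.63 points. Both match the stated 8.6 points and d = 0.43.

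**Step 5: does site clustering inflate this contrast?** Write a patient's outcome as a site effect, plus the treatment effect if treated, plus individual error. Within a site, the difference between arms subtracts the same site effect from itself. With both arms at each site (72 per group per site are planned) and site in the analysis, the pooled contrast averages these within-site differences. Its variance depends on the within-site SD and the number per arm, not on the spread between sites. The SD of 20 is the value that the plan itself applies within one site.

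**Step 6: the pooled figure without the 1.5.** n per arm = 128. Detectable d = 2.802 × √(2/128) = 2.802 × 0.125 = 0.350, or 7.00 points (noncentral t: d = 0.352, 7.03 points). The standard error is 20 × 0.125 = 2.5. At 8.6 points, 8.6/2.5 − 1.96 = 1.48, so power is 93%. At 10 points, 10/2.5 − 1.96 = 2.04, so power is 98%.

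**The case against.** The strongest reply is that nothing here makes the trial too small. The body of the article plans 144 per site and recruitment of 300. The 76% arises only if the Abstract overrides both sections, and even then the loss is about 4 percentage points. The design effect errs on the safe side, appears only in a conditional sentence about pooling, and sets no enrolment number. All of this stands.

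Some inflation could also be defended on other grounds. Nurses deliver the intervention, so outcomes may cluster by nurse, and the treatment effect may differ between sites. That also stands as a possibility, but the Sample Size section gives only clustering within the site. The Randomization section does not mention stratification by site, so the site effect cancels exactly only with balance within sites; otherwise site must be in the model.

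Three stronger readings are tempting and not supported:

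- **That 300 is a third, contradictory sample size.** It is a recruitment figure built on approximate wave sizes. Elective patients consent and are registered before surgery, and are randomized only after passing the ward screen; Feasibility expects some to fall out. So 300 recruited and 288 randomized can coexist, although the article does not say how they relate.
- **That the stated sizes do not fit the design.** The 64, 128 and 144 reproduce and suit individual randomization.
- **That 1.5 is too small.** With 128 per site it implies an intracluster correlation of (1.5 − 1)/127 = 0.004, and one could argue that larger values are plausible. The article gives no intracluster correlation to judge by, and the question lapses if the inflation does not apply.

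**Conclusion.** The concern holds on two limited counts. The Abstract's 256 randomized conflicts with the Sample Size section, where 256 are completers and 288 randomized are implied. If the Abstract were followed and 10% were lost, per-site power for 10 points would be about 76% against the stated 80%. The pooled detectable difference of 8.6 points (d = 0.43) rests on a reason that does not fit the design. On the plan's own inputs, 256 completers detect about 7.0 points (d = 0.35) at 80% power, and power at 8.6 points is about 93%.

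The second result assumes SD 20 within sites, both arms at each site in about equal numbers, site accounted for in the analysis, a common treatment effect across sites, and no clustering by nurse. A reader might infer from either count that the trial as planned is underpowered. The documents do not support that: the per-site sizes are correct, the body sections plan at least 288, and the design-effect error understates pooled power.

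**What to change.** State 288 randomized (144 per site) and 256 evaluable in the Abstract and wherever a total appears. Add a sentence in Feasibility saying how the 300 recruited relates to the 288 randomized. In the Sample Size section, restate the pooled detectable difference as about 7.0 points (d = 0.35) at 80% power with site in the model. Alternatively, keep a design effect and justify its size on grounds other than site clustering, such as clustering by nurse or variation of the treatment effect between sites. The cost is a few sentences and one or two restated figures; no patients are needed beyond those already planned.

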##### Recruitment

Strategies previously developed will be applied [3,6]; RAs will screen preoperative surgical patient lists daily. Anesthesia, CaVS, and medicine services will contact the RAs for all CaVS admissions through emergency and new consultations. Eligible patients will be approached and invited. Patients providing informed consent will be registered via the Interactive Web Randomization System (IWRS), a 24-hour, central, computerized, secure (ie, password-protected), Web-based registration/randomization service at the Population Health Research Institute, and baseline data will be collected. Patients undergoing urgent surgeries will be approached postoperation.

##### Randomization and Allocation

Blocked randomization (ie, randomly assigned block sizes) will be used to achieve balanced allocation of intervention and control groups. The randomization allocation list will be prepared by Population Health Research Institute statisticians and integrated into the IWRS system. Upon transfer to the surgical ward (ie, post-ICU), the SVN will assess consented patients using the CAM. If CAM scores do not indicate cognitive impairment or delirium and the patient remains eligible, they will be randomly allocated by the IWRS.

#### Feasibility

Our technology partners have contributed equipment and personnel time, in-kind, such that we are able to intervene and follow up on 15 patients at one time per site throughout the study until 30 days follow-up, at which time equipment will be returned to each hospital site for cleaning and reset. Therefore, the RCT (Phase 2) will be executed in five serial, parallel waves of approximately 30 patients per site. In 2014, there were 2311 and 1974 CaVS performed at Hamilton Health Sciences, Canada, and the Liverpool Heart and Chest Hospital, the United Kingdom, respectively. Planned recruitment will occur at a rate feasible for SVN time and access to the surgical populations at both sites. Patients will be enrolled during a 3-week period, with the last week of each recruitment month available for additional patient registrations as needed to accommodate those not meeting postop eligibility. Each site will target recruitment of 14 cardiac and 16 vascular patients during 3 weeks of recruitment—10 patients per week, per site. Allowing for a 25% refusal rate, lost opportunities, and competing studies, this still provides access to 20 patients at Hamilton Health Sciences and 17 patients at the Liverpool Heart and Chest Hospital. Since participant recruitment is only limited by prototype availability, our proposed recruitment target and timeline is feasible and recruitment of 300 participants will be completed in 10 months’ time.

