###### Hospital-to-Home Remote Monitoring and Support

The eTrAC program is a tablet-based solution that combines clinical software for effective care management with Bluetooth-enabled, patient-monitoring devices measuring SpO_2_, blood pressure, temperature, blood glucose, and weight [83]. Philips eTrAC allows clinicians to monitor discharged (ie, at-home) patients’ vital signs status from the hospital (Protect), and then prioritize them for required interventions (eg, signs of sepsis evident) based upon a combination of customized/standardized intervention rules [83]. eTrAC also features customizable, interactive patient symptom and self-report surveys to inform postoperative support and management. SMArTVIEW-specific surveys include postop daily symptoms, wound monitoring, sleep, nutrition, medication, quality of life, and patient satisfaction. Interactive modules assisting patient orientation to the system are also included. The clinician interface for the eTrAC program is eCare Coordinator (eCC), a cloud-based software tool designed to maximize efficiency through risk prioritization— patients are assigned overall scores calculated from weighted scores of self-report surveys, measurements, issues, risk of readmission, and discharge date if within the last 30 days. The overall score generated allows clinicians to manage large patient populations by triaging their interventions based on potential patient need (ie, those with the highest scores are seen first). Through eCC, clinicians can remotely manage patients, view and interpret results (eg, vital signs and symptom and reflexive surveys), follow up and intervene as needed, conduct video visits with patients, and document all patient interventions and observations.

The SVN will employ the eTrAC program to facilitate daily virtual check-ins and counseling, daily vital signs monitoring and triage, and review of interactive symptom and reflexive surveys (Access, Inform, Protect, Connect) [83].

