	**Patient and family pain education and hospital-to-home orientation** **(ward day 2)**	
		The SVN will facilitate a 2.5-hour hospital-to-home orientation session implemented at the convenience of the patient, supports (eg, family, friends, and caregivers), and clinical workflow.
		This orientation will focus on the eTrAC^c^ tablet-based applications, the PRAS^d^ educational video, and Restore.
		Following the orientation, the SVN will invite and answer questions.
	**Receipt of SMArTVIEW hospital-to-home package and skills rehearsal** **(day prior to discharge**)	
		On the day prior to discharge, patients will receive their hospital-to-home packages from the SVN, including eTrAC tablet-based solutions, instructions for monitoring vital signs at home, eTrAC 30-day application schedule for monitoring vital signs, SVN video visits, and daily recovery symptom and reflexive surveys.
		Upon receipt of this hospital-to-home package, the SVN will facilitate a 30-minute checklist-oriented rehearsal of all eTrAC features; the SVN will also invite and answer questions.

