	**Patient monitoring and virtual check-ins** **(first 30 days postdischarge)**	
		The SVN will perform daily 15-minute virtual check-ins—eTrAC video visits—with patients at home from the hospital via eCC, per hospital-to-home package instructions.
		Virtual check-ins will include review of priorities flagged in eCC, review of vital signs and symptom and reflexive survey data, postop pain assessment, and discussion of any patient/SVN concerns.
		Issues identified—via eCC risk stratification or SVN assessment—that require intervention, but are out of the scope of SVN practice, will be escalated to the most responsible clinician.

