	**SMArTVIEW-Restore** **(0 to 7 weeks postdischarge)**	
		During recovery, participants will engage the Restore time-release, self-guided, online curriculum (described previously).
		Restore is structured according to seven weekly asynchronous modules, consisting of two to seven activities each.
		Restore is designed to constitute 2-3 hours of online activity, weekly.

^a^SMArTVIEW: Self-MAnagemenT—VIsion for patient EmpoWerment.

^b^SVN: SMArTVIEW Nurse.

^c^eTrAC: Transition to Ambulatory Care.

^d^PRAS: pain relief after surgery.

^e^eCC: eCare Coordinator.

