##### Follow-Up

The SVN will collect outcome data for intervention and control groups following random allocation through discharge. Once in the community, patients in both groups will record their BPI-SF pain scores daily for 8 weeks using the tablet-based solutions. Data on 30-day event rates (ie, major postop complications) and hospital readmissions for both groups will be collected by a blinded RA via telephone interview at 30 days postoperation. At 3, 6, 9, and 12 months, additional telephone interviews conducted by the RA will assess (1) functional status, (2) depressive symptoms, (3) CPSP, and (4) patient-level cost of recovery (ie, AHCR).

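### Home equipment is returned at 30 days, but daily pain scores are to be recorded on the tablet for 8 weeks, so at least the intervention arm has no described way to record pain in the later weeks

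*Protocol article*

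**What the plan says.** The Follow-Up section of the protocol article fixes both the instrument and the duration: once in the community, "patients in both groups will record their BPI-SF pain scores daily for 8 weeks using the tablet-based solutions".

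The Feasibility section describes equipment contributed by the technology partners and gives its capacity: "we are able to intervene and follow up on 15 patients at one time per site throughout the study". It then limits how long each patient has the equipment, which is kept "until 30 days follow-up, at which time equipment will be returned to each hospital site for cleaning and reset". Five successive waves of about 30 patients per site are built on this, with 300 participants recruited in 10 months.

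On what the home equipment is, the section on hospital-to-home monitoring states: "The eTrAC program is a tablet-based solution that combines clinical software for effective care management with Bluetooth-enabled, patient-monitoring devices". Table 2 lists the contents of the package handed over before discharge, "including eTrAC tablet-based solutions, instructions for monitoring vital signs at home, eTrAC 30-day application schedule for monitoring vital signs".

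Other periods run past day 30 or count from a different start. The Abstract says "The SMArTVIEW intervention will run from surgical ward day 2 until 8 weeks following surgery". In Table 2, monitoring and check-ins cover the "first 30 days postdischarge" and Restore covers "0 to 7 weeks postdischarge".

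The date of the primary endpoint is itself given in two ways. It is 8 weeks in the Abstract and Table 3, and 30 days in Trial Design, Primary Outcome and Primary Analyses.

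**The concern.** If the tablet goes back with the rest of the kit at 30 days, a patient cannot go on entering a daily score on it until week 8. The article names no substitute. The telephone interview at 30 days covers events and readmissions, and the next calls are at 3 months. The Abstract lists a week 8 assessment, but Follow-Up gives no means for it other than the tablet.

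The loss would not be scattered missingness. It would be the same block of late days for every patient whose kit is returned. Primary Analyses notes that mixed models do not need complete data on each patient. That does not help if a whole arm has no scores at week 8, because the week 8 contrast would then rest on extrapolation from earlier weeks. If controls kept their tablets and intervention patients did not, the gap would be differential by arm.

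**Working it through.** **1. Is the tablet in the returned equipment?** Feasibility says equipment, not tablets. The monitoring section defines the home system as tablet-based with connected devices, and Table 2 puts it in the take-home package. Resetting fits a programmed device, and nothing exempts the tablet. For the intervention arm the inference is strong. For controls the article gives neither a source nor a return date.

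**2. Diary days after return, common clock.** Inputs: 8 weeks = 56 days (Follow-Up); return at day 30 (Feasibility).
- 56 − 30 = 26 days; 26/56 = 46%.

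**3. Diary days after return, different clocks.** The documents use surgery, randomization and discharge as starting points, and Feasibility does not say which applies to the return. Assumptions, not in the documents: randomization 1 to 3 days and discharge 5 to 10 days after surgery.
- Shortest gap: return 30 days after discharge on day 10 is day 40; 8 weeks after surgery is day 56; 56 − 40 = 16 days.
- Longest gap: return 30 days after surgery is day 30; 8 weeks after discharge on day 10 is day 66; 66 − 30 = 36 days.
- The minimum of 16 exceeds 14, so the last 14 days before week 8, and hence the final weekly average, always fall after return.

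**4. The 30-day endpoint.** Primary Outcome averages the 14 days up to 30 days after randomization.
- Return counted from randomization or discharge: nothing, or essentially nothing, is lost.
- Return counted from surgery, with randomization 1 to 3 days later: the window ends 1 to 3 days after return, so 1 to 3 of 14 days are lost.

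**5. Effect on the timeline of keeping tablets to week 8.** The stated figure is for completing recruitment, so the count stops when the fifth wave has enrolled. Inputs: 21 days of enrolment per wave, or 28 with the spare week; 30.44 days per month.

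| Equipment held | Recruitment ends | Months |
|---|---|---|
| 30 days | 4 × 51 + 21 = 225 to 4 × 58 + 28 = 260 days | 7.4 to 8.5 |
| 56 days | 4 × 77 + 21 = 329 to 4 × 84 + 28 = 364 days | 10.8 to 12.0 |

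The 30-day hold fits the stated 10 months. Under strictly serial waves the 56-day hold exceeds it by 0.8 to 2.0 months.

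Rolling reuse by intervention patients only: 5 waves × 30 = 150 patients per site, about 75 in the intervention arm. 75/15 = 5 cycles; 5 × 56 = 280 days = 9.2 months, within 10 even with the last hold counted. This is not the serial-wave plan, and it supplies no tablets to controls.

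**The case against.** The strongest defence is that the 30-day return concerns the vital-signs kit, whose schedule is also 30 days, and that three sections place the primary endpoint at 30 days, when the pain data would be in hand. Much of this stands, and it rules out several stronger readings that a reader might infer:

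- **That the primary outcome is lost outright.** This is so only under the 8-week definition. Under the 30-day definition at most a few days of the window are cut.
- **That no patient in either arm has an instrument in weeks 5 to 8.** The documents do not say that control tablets come from this pool or go back at day 30.
- **That 15 kits contradict waves of 30.** With balanced allocation, 30 patients per wave means about 15 in the intervention arm. What is missing is the source of the control tablets.
- **That 10 months is achievable only with a 30-day return.** Rolling reuse of intervention kits could keep within it.
- **That Restore must stop.** It is web-based and only optimized for tablet, so another device may serve.
- **That missingness will differ by arm.** This is possible, but depends on the unstated control arrangements.

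The defence does not remove the core conflict. Nothing separates the tablet from the equipment that goes back, and no other daily BPI-SF route is given for the weeks after return.

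**Conclusion.** The concern holds in this form: Follow-Up and Feasibility cannot both be carried out as written for the intervention arm, and the article is silent on the control arm. About 26 of 56 diary days (46%) fall after return on a common clock, or 16 to 36 days under the assumed timings of randomization and discharge. The last 14 days before week 8 are lost in every case examined. If the 8-week endpoint of the Abstract and Table 3 is primary, it lacks data in at least one arm. If the 30-day endpoint is primary, its data are complete or nearly so, and the damage is confined to the week 5 to 8 series.

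This rests on reading the tablet as part of the returned equipment, which is well supported for intervention patients but not stated in so many words. The sample-size figures are not affected. The point goes beyond missing detail because the article gives both the collection method and the return date, and scores not collected cannot be recovered later.

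**What to change.** Before enrolment:

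1. State which items are returned, from which starting point the 30 days are counted, and where control-arm tablets come from and when they go back.
2. Collect daily BPI-SF through week 8 by one route, identical in both arms, that does not depend on the returned kit: for example a web link or telephone diary, with paper as back-up. The cost is a simple diary set-up and protocol wording. The small downside is some variation in recording device.
3. Alternatively, leave tablets with patients in both arms to week 8 and recheck the schedule. Strictly serial waves would end recruitment at about 10.8 to 12.0 months instead of 10. Rolling reuse of intervention kits could stay within 10, but the control tablets must then be supplied separately.
4. Reconcile the return date with the monitoring and Restore periods in Table 2 and with the 8-week intervention period in the Abstract.
5. Settle the 30-day versus 8-week primary endpoint in the same amendment, since the device date and the endpoint date depend on each other.
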